### Research questions

I.Analysis and operationalization of barriers to primary PC provision by GPs in the German healthcare context on a structural, educational, process, and economic level: Which mechanisms and formal regulations impede routine embedding of PC provision in GPs everyday clinical practice at individual and collective level?II.Identification and operationalization of concrete measurable actions to improve the implementation of primary PC delivery by GPs: Which measures will have the potential to facilitate integration of end of life care with a generalist caseload and to enable the GP and his practice team to provide high quality PC to their patients? Which measures will be suitable to promote collaboration with other care providers relevant for PC delivery?III.Testing and evaluation of a tailored intervention package for the facilitation of primary PC delivery by GPs in Germany: What is its practicality, as well as its impact on care and patient-relevant outcomes? How well does it score compared to other models of GP involvement in PC delivery?

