**Table 1 Tab1:** Target/ study population detailed for each work package of data collection

Work package	Target population	Proposed sample size	Sampling strategy
Ethnographic research	GPs; GPs assistants, professional caregivers	*n* = 30	The Institute of General Practice’s education and research network of *n* = 250 general practices; theoretical sampling contrasting: rural vs. urban; single vs. joint practice; specific palliative education vs. nonspecific palliative education
Secondary analysis	GPs, GPs assistants, professional caregivers	interviews: *n* = 52 group discussions: *n* = 3	Existing data set of interviews / one focus group with GPs conducted within the ELFOP project; all interviews and the focus group are included
CIT	GPs, GPs assistants, professional caregivers, patients and relatives	*n* = 16	Theoretical sampling contrasting: rural vs. urban; diagnosis; single vs. joint practice; men vs. women
Analysis of Health insurance claims data	GPs’ patients identified as being in need of PC	not applicable	Health insurance claims data: all AOKN and BARMAR insured persons in Lower Saxony with palliative billing codes
PAR	GPs, community nursing teams, patients and informal carers, other relevant PC providers	not applicable	Theory-based purposive sampling [55]
Delphi study	GPs’ professional representatives and other relevant experts for health policy decision making and healthcare planning	*n* = 30	DEGAM; DGP; GPs’ chairmen / quality circles; the Institute of General Practice’s close links with GPs’ professional boards and associations (Hausärzteverband)
Consensus workshops	GPs’ professional representatives; health insurers; experts for medical education; and other relevant experts for health policy decision making and healthcare planning	*n* = 20	Two groups with approximately 10 participants each; theory-based purposive sampling [55]
Implementation of the intervention package	GPs’, community nursing teams, health insurers; and other relevant experts for health policy decision making and healthcare planning	not applicable	Exemplary test region in Germany (Lower Saxony) involving n = 8 general practices, as well as all relevant service providers and stakeholders in the respective region

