Questionnaire survey (Summative evaluation)	GPs’, community nursing teams, health insurers; and other relevant experts for health policy decision making and healthcare planning	*n* = 130	Service providers, insurers, and other local stakeholders involved in the implementation of the tailored intervention package (Phase II) and from two exemplary other regions in Germany
Patient-relevant outcomes (Summative evaluation)	Patients and informal carers	standardized scales *n* = 32 interviews *n* = 16	Patients and informal carers attended by general practices who are involved in the implementation of the tailored intervention package (Phase II) and from two exemplary other regions in Germany

Fourth, *secondary analysis of health insurance claims data* of the AOK – Die Gesundheitskasse für Niedersachsen (AOKN, statutory health insurance) and BARMER (statutory health insurance), and from the GPs’ office software will serve to describe the morbidity and service usage of patients, assess patient-relevant outcomes such as hospital admissions, estimate the time investment and costs for the provision of primary PC by GPs, and to draw inferences on the relevant laws, professional regulations, and reimbursement systems (see Table 2).

**Table 2 Tab2:** Outcomes, comparators, and data sources

Outcome	Measure(s), indicator(s)	Data source
Patient-related outcomes		
Quality of life	Physical and psychosocial wellbeing, social support, financial strain	Standardized quality of health / care related measures such as POS^a^; QODD^b^; QUELC^c^
Quality of care	Unplanned hospital admissions	Health insurance claims data
Service usage and time investment		
Service usage	GPs’ consultations and home visits; prescriptions (medication, medical aids, interventions); referral to specialists and other service providers; out-of-hours contacts; emergency interventions	Health insurance claims data GP’s office software
GPs’ time investment	Time dedicated to assessments, home visits, telephone consultations, physical care, and psychosocial care	Time registration (ethnographic field research)
Impact on GPs’ and practice staff’s ability and capacity to deliver primary palliative care		
Quality of palliative care delivery	GPs’ and practice staff’s appraisal of the quality of PC provided to their patients	Organizational ethnographic field research including individual and group interviews

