First, *Participatory Action Research* (PAR) [33] will be undertaken with general practices, community nursing teams, patients and informal carers, as well as other relevant PC service providers to define adequate operationalization of PC processes and quality outcomes, and to condense a set of service development statements [34, 35].

Second, a *nation-wide consensus Delphi study* will be undertaken with GPs and their professional representatives such as the GPs’ professional federation, the Medical Chamber, and the German association of general practice (DEGAM) to seek expert consensus on these service development statements.

Third, *consensus workshops* will be conducted in the follow-up of the *Delphi study*, using the *Nominal Group Technique* [36] to elaborate a strategic action plan on how to put the service development statements into practice. Workshop participants will be key representatives from the practical, education, economic, and policy sphere, as well as representatives of patients and relatives. Data collected during this phase will be integrated during analysis (see [2, 37]) to design the tailored intervention package.

Finally, an intervention package will be developed for enhancing the integration of PC provision into general practice, drawing on the example of the Gold Standards Framework for Palliative Care [12], but adapting it to the German context. A participatory framework and consensus building techniques will be applied to promote ownership of the developed elements and to enhance commitment among the relevant stakeholders.

***Phase III – Implementation and evaluation:*** The intervention package developed in phase II will be implemented and evaluated in an exemplary test region in Lower Saxony.

First, *formative evaluation* will use an organizational ethnographic approach including individual and group interviews with relevant stakeholders to (a) test the feasibility and acceptance of the intervention in practice, and (b) to compare the intervention to two exemplary other regions in Germany with different approaches to generalist and specialist PC provision in terms of contracts with health insurance funds, different roles of GPs in the local delivery of PC (e.g. Westphalia-Lippe).

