Second, *summative evaluation* will be accomplished to assess the effects of the intervention on patient care in terms of physical, practical, and psychological outcomes. Data sources will be a questionnaire survey among the relevant stakeholders involved in PC provision; analysis of clinical and health insurance funds routine data to assess the effects on patient care, service usage, and costs of care; and perceptions of patients and relatives regarding the outcomes of care using established instruments such as the Palliative Outcome Scale [38] (Table 2).

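### On the summative survey (n = 130) and the patient/carer scales (n = 32), a package effect cannot be separated from existing differences between regions, yet effects and impact are promised

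*Protocol article*

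**What the plan says.** Table 1 of the protocol article places the implementation in one "Exemplary test region in Germany (Lower Saxony) involving n = 8 general practices". For the patient-relevant outcomes of the summative evaluation it gives "standardized scales *n* = 32 interviews *n* = 16", and the source entry begins "Patients and informal carers attended by general practices who are involved in the implementation of the tailored intervention package (Phase II) and from two exemplary", with the comparison regions completing the phrase. The row for the questionnaire survey (n = 130) uses the same three-region source.

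The Phase III text describes the two other regions by how they differ, in contracts with health insurers and in the role of GPs. The aim "to compare the intervention to two exemplary other regions in Germany with different approaches to generalist and specialist PC provision" is part (b) of the formative evaluation. The summative evaluation "will be accomplished to assess the effects of the intervention on patient care in terms of physical, practical, and psychological outcomes".

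Research question III has two parts: "What is its practicality, as well as its impact on care and patient-relevant outcomes" and "How well does it score compared to other models of GP involvement in PC delivery". Under Expected results, the product is a pilot-tested package described as evidence-based, with knowledge of its impact on patient-relevant outcomes.

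The survey is to be analysed descriptively, and the scales according to their own scoring instructions. Routine clinical and insurance data are a further source for effects on care, service use and costs.

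**The concern.** For the survey and the scales, every respondent exposed to the package is in one region, and every unexposed respondent is in a region with a different care model. The article describes no earlier measurement on these instruments and no adjustment for case mix. A between-region difference would therefore contain the package, the insurer contracts, the local infrastructure and the mix of patients, with nothing to separate them.

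The article's own background section says that practice depends heavily on regional structures, so outcomes should be expected to differ between regions without any package.

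At stake is the impact part of research question III. A regional difference could be read as an effect of the package, or could hide one, and the result would then feed a national action plan.

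**Working it through.** **1. The plan's own figure.** There is nothing to reproduce. Table 1 states n = 32 without alpha, power, effect size, SD or a split by region. The Sample size calculation section justifies only the survey's 130, and on grounds of content.

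**2. What 32 respondents can show.** Inputs: total 32 (Table 1). Assumed: two-sided alpha 0.05, SD = 1, independent respondents, patients and carers taken together, and three possible splits of test region v the two others combined.

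Detectable difference at 80% power = (1.960 + 0.842) × √(1/n₁ + 1/n₂). The 95% half-width = 1.960 × the same root.

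| Split | √(1/n₁ + 1/n₂) | Detectable difference, normal | Detectable difference, t-based | 95% half-width, normal | Power for 0.5 SD, normal |
|---|---|---|---|---|---|
| 16 v 16 | 0.354 | 0.99 SD | 1.02 SD | 0.69 SD | 29% |
| 11 v 21 | 0.372 | 1.04 SD | 1.08 SD | 0.73 SD | 27% |
| 8 v 24 | 0.408 | 1.14 SD | 1.18 SD | 0.80 SD | 23% |

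Detecting 0.5 SD with 80% power would need 63 per group before any clustering. Reporting patients and carers separately makes each comparison smaller still.

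**3. A larger sample would not cure the regional problem.** Suppose a share ρ of the outcome variance lies between regions. With one region against two, the regional part of the variance is ρ × (1 + 1/2), whatever the number of respondents. The 95% half-width then cannot fall below 1.96 × √(1.5ρ):

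| Assumed ρ | Smallest half-width |
|---|---|
| 0.01 | 0.24 SD |
| 0.02 | 0.34 SD |
| 0.05 | 0.54 SD |
| 0.10 | 0.76 SD |

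This counts only random variation between regions. It leaves out the systematic differences in contracts and GP roles by which the article describes the comparison regions. The same limit applies to a scaled outcome from the 130 survey respondents.

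**4. Can the routine data supply the missing contrast?** Four statements have to be set side by side.
- Phase I analyses claims and office-software data, including hospital admissions and service use, before the package exists.
- Table 1 describes the claims data as covering the insured persons of two insurers in Lower Saxony with palliative billing codes. No claims data from the comparison regions are described.
- The package reaches 8 practices. No link between the claims data and those practices is stated.
- The summative paragraph uses routine data for effects, and the analysis section names regression and survival methods. Neither names a before-after or between-group contrast.

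The data could therefore support a before-after comparison, but the article does not set one out. Entry by billing code adds a difficulty: the Discussion expects earlier identification of patients in need of palliative care, which could change who is coded. Claims data also cannot provide the psychological outcomes that the summative evaluation names.

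**The case against.** Several points on the other side stand.

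- **The regional comparison has a legitimate purpose.** The sentence on regions with different approaches belongs to the formative, interview-based evaluation, and the second part of research question III asks how the package compares with other models. A reader might infer that choosing different regions is itself an error. It is not: for that question the difference is the contrast of interest. Only the impact part is exposed.
- **The evaluation is wider than 32 people.** A reader might infer that it rests on 32 respondents with nothing measured beforehand. The documents do not support this. The 32 applies to the scales, the claims data have no fixed size, and Phase I claims and office-software data precede implementation.
- **The article is a condensed account.** A baseline for the survey and scales can be called not described; it cannot be called absent.
- **No hypothesis test is planned for the survey or the scales.** The power figures are a guide to precision. They do not show that a planned test fails.
- **Feasibility is a stated purpose.** The implementation phase is designed to test acceptance, feasibility and applicability, and the package is called pilot-tested. That purpose is sound, but it does not support the words effects and impact for these outcomes.
- **A before-after measurement remains uncontrolled,** and it adds burden in a setting where the ethics section asks for care over burden.

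**Conclusion.** The concern holds for the summative survey and the standardized patient and carer scales. On these outcomes package and region are fully confounded, no baseline or case-mix adjustment is described, and the stated aims go further than the comparison can support. On the scales the detectable difference is about 1.0 to 1.2 SD (normal and t-based values over the three splits). This assumes those splits, SD = 1 and no clustering. The confounding depends on none of these assumptions.

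It does not follow that research question III is unanswerable as a whole. Practicality and the descriptive comparison of care models are within reach, and the routine data may allow a better contrast if one is set out.

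**What to change.** Amend the summative evaluation paragraph and the two summative rows of Table 1.

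1. **Benchmark and wording.** State that the survey and scale comparison with the two other regions is a descriptive benchmark of care models and does not estimate the effect of the package. For these outcomes, replace effects, impact and evidence-based with feasibility and preliminary change, including in research question III and Expected results. This costs only a more modest claim.
2. **Pre-launch wave.** Give the same stakeholder questionnaire in the 8 practices before launch and, where burden allows, one common patient instrument. Report the before-after change with 95% intervals, patients and carers separately. State that the change is uncontrolled and that the patients before and after are different people. The cost is one extra wave of a questionnaire already planned, with some respondent burden. It has to happen before launch; the article reports Phase I as only partly complete.
3. **Routine data.** Where claims or office-software data can be linked to the 8 practices, use the pre-launch period as baseline, with other Lower Saxony practices in the same data as a concurrent comparison. Say how a change in who receives a palliative billing code will be handled. The cost is the linkage work. If linkage is not possible, say so and keep the claims results descriptive.

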### Sample size calculation

Phase I: For the ethnographic field research the participation of *N* = 8 GPs, GP assistants and other medical professionals was planned considering methodological arguments of theoretical sampling when contrasting practices characteristics such as rural vs. urban, single vs. joint practice, men vs. women. At least *N* = 16 interviews following the Critical Incident Technique were proposed which relates to the methodological experience that data saturation in qualitative analysis via Grounded Theory. Data collection will end once data saturation is obtained which will be the case when no more new or valuable information can be attained, further coding is no longer feasible, and once the study can be replicated [39]. This usually takes place after 12–15 interviews. The sample size of secondary analysis of qualitative data from ELFOP is pre-determined due to the retrospective design of the sub project. The sample size of the secondary analysis of health insurance claims data is not applicable and will be defined by the amount of specific data sets of the current insured persons of the AOKN and BARMER.

Phase II: Reflecting the current literature on successful Delphi studies, *N* = 30 participants who complete each Delphi round are planned. Due to the expected drop-out of 60% during the course of the Delphi assessment, probably three times as many participants will be initially invited to this sub project [18]. The final consensus workshops aims to include *N* = 20 stakeholders following a theory-based purposive sampling [40].

Phase III: For the questionnaire survey in terms of the summative evaluation a participation of *N* = 130 key stakeholders of local (primary) palliative care delivery from the practical, education, economic, and policy sphere, as well as representatives of patients and relatives is proposed based on content-related reflections taking the accumulated sample size of the prior subprojects into account.

### Methods of data analysis

***Phase I + III:***
*Analysis of qualitative data* (ethnographic field research, CIT, secondary analysis of interviews and focus group), as well as for the formative evaluation during the *implementation phase* (organizational ethnographic approach with individual and group interviews) will be guided by the methodology of Grounded Theory. For each qualitative data-subset (field notes, interviews, focus group), Strauss and Corbin’s single coding paradigm [41] will be used to identify salient determinants and mechanisms of relevance to primary PC delivery in general practice. To ensure inter-subjective validity and reliability, qualitative data will be analyzed independently by the members of the junior research group and discussed within the team until consensus on core categories will be reached. Analysis of health insurance claims data and GPs’ office software will follow the guidelines for best practice of secondary data analysis [42]. For quantitative data analysis univariate and bivariate descriptive methods as well multivariate methods (e.g. logistic regression or survival analysis [43, 44]) of empirical social research will be used. The findings from the different data sources within the *theoretical phase* will be triangulated to draw inferences on the structural, economic, and interactional mechanisms that either hamper or facilitate PC delivery in general practice.

***Phase II:*** A characteristic feature of *Participatory Action Research* is community and practice partners’ participation also in the phase of data analysis [45]. Mutual reflection, shared learning and co-construction of meaningful outcomes are key elements of this process; for this aim, pragmatic and comprehensible methods are recommendable such as thematic or content analysis, or the single coding paradigm. A stepwise approach to data analysis will be conducted in working groups composed of academic staff and representatives from the field [45]. Outcomes of the *Nominal Group Technique employed during the consensus workshops* will be analyzed using quantitative (descriptive comparison between ranks and weights of ideas and statements) and qualitative methods (combination of structured-thematic and formal qualitative content analysis) [46].

The Delphi study and the questionnaire survey will be analyzed using descriptive statistics (percentages, measure of central tendencies such as mean and median values, and measures of dispersion such as variance, interquartile ranges, and standard deviation). For the Delphi study, results of concluded survey rounds will be processed to provide feedback to the participants in the subsequent round [47]. If necessary, service development statements will be modified based on the experts’ responses in order to inform the questionnaire for the next survey round and hereby improve the degree of consensus within the expert panel. For the development of the tailored intervention package, data from the different sources in the modelling phase will be integrated in accordance with the framework for the design of complex interventions [26] and the corresponding guidance for synthesizing and triangulating mixed methods data (48). Following the recommended phases of the mixed methods analysis process [48], a package of expedient interventions will be proposed and elaborated based on the data collected during the participatory process, will be translated into service development statements, and consented during the subsequent Delphi survey and consensus workshops.

Statistical analysis will be compared and contrasted with qualitative data on direct and indirect costs resulting from organizational ethnographic research including individual and group interviews using triangulation. Standardized patient-related outcomes such as Palliative Outcome Scale [38] or Quality of Dying and Death questionnaire [49] (Table 2) will be analyzed according to the instructions for scoring, analysis, and interpretation of responses indicated by the authors in the instruments’ manual, on the respective website, or in key publications.

All qualitative analysis will be conducted using software for qualitative text analysis (MAXQDA®). Quantitative data will be analyzed using IBM SPSS Statistics (Version 24) and R (Version 3.3.0).

